### Cox regression analysis

ANISA data were initially analysed using time-to-event Cox hazards regression models, as described previously.^32^ This same approach will be applied to the pooled data across the AFRINEST and ANISA studies. We will investigate the association between finding a sign of PSBI from the first visit to the end of 60 days after birth and the risk of all-cause mortality compared with not finding such a sign. Infants who were never visited or who died before a CHW visit will be left censored, and exposure periods of unknown status pertaining to the presence of signs of PSBI before the first visit will be eliminated. The period of risk for mortality will be defined as extending for 7 days after finding a sign of PSBI; a sensitivity analysis will be performed using a 14-day period of risk for mortality. We previously showed that for the ANISA data, results were similar for these two periods of risk for mortality.^32^ We will also calculate Kaplan-Meier probabilities of mortality over the young infant period. We will use Cox regression analysis to examine patterns of CHW identification of each sign as follows: a single sign found alone, the sign found with at least one other sign or any sign(s) found other than the particular sign compared with not finding any sign in association with all-cause mortality. Cox regression will also be used to examine the association between the presence of clinical signs and the occurrence of mortality during time frames of the first CHW visit to the end of day 3 (days 0 to <3), the first visit to the end of day 7 (days 0 to <7) and day 7 to the end of the 60th day (days 0 to <60). Analyses will be adjusted for covariates that are in common across all datasets.

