**Methods and analysis:**

We will create a dataset that integrates data from population-based studies globally with similar designs that have examined the presence of signs of PSBI identified by frontline health workers throughout the young infant period (days 0 to <60) and that have also recorded infant vital status. We will conduct pooled, individual-level analyses of the frequency of identification of signs individually and in combinations and will conduct three types of analyses of association of signs of PSBI with mortality: (1) case fatality, which has been used in a multisite study of mortality risk associated with signs of PSBI in young infants in Africa; (2) Cox regression, which will enable time-varying analysis of exposure in relation to mortality, as has been done in a multisite study in Asia and (3) machine learning analysis, which has not previously been applied to any of the available data.

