Recognising the need to provide guidelines on the identification and management of infections in young infants, based on several studies of clinical signs of illness associated with a need for hospitalisation of young infants during days 0 to <60,^7^,^13^ the WHO published Integrated Management of Childhood Illness (IMCI) in 2014, which included 7 signs of PSBI indicating the need for referral of sick young infants for hospital care.^14^ These signs were: not able to feed at all or not feeding well, convulsions, severe chest indrawing, high body temperature (38°C or above), low body temperature (less than 35.5°C), movement only when stimulated or no movement at all, or fast breathing (60 breaths per minute or more). In 2015, WHO further recommended outpatient treatment of infants aged 7–59 days who present with isolated fast breathing with oral amoxicillin without a referral,^15^ which was included in the 2019 IMCI chart booklet for young infants.^16^ WHO guidelines currently give equal importance to the other six PSBI signs. However, implementation of IMCI would be further aided by the identification of young infants with signs of illness at a lower risk for mortality who could potentially be treated on an outpatient basis. In addition, using mortality as the outcome in assessing the risk associated with signs of PSBI rather than the need for hospitalisation may enhance policy relevance.

We aimed to identify and pool individual subject data from studies globally that used similar methods to systematically assess infants for signs of PSBI, conducted by community-based frontline health workers, while also recording vital status during the young infant period. We will examine associations of signs individually and in combination with mortality to further define a level of risk for mortality and inform WHO IMCI global guidance for the assessment and management of young infants.

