Baseline data collection	CHWs collected data using standardised questionnaires during pregnancy and home visits after childbirth. The first visit was as soon as the pregnancy was confirmed, and the second was 2 months before the expected delivery date. At the first home visit after the birth of liveborn infants, CHWs/CHEWs recorded pregnancy outcomes, date of birth, place of birth, birth attendant, postpartum status of the mother, participant demographics, home environment, birth weight, postpartum neonatal characteristics at birth, history of any complaints and examination of the baby to identify any signs of illness. CHW/CHEWs recorded maternal deaths, miscarriages, stillbirths and infant deaths in the first 2 months after birth.	CHWs collected data using standardised questionnaires during pregnancy and the first home visit of liveborn infants on participant demographics, home environment, pregnancy and birth history, postpartum maternal characteristics and neonatal characteristics at birth.
Clinical sign assessment (see table 2 for definitions of signs)	CHWs in DRC and Kenya and CHEWs in Nigeria visited infants at home on days 0, 2, 6, 13, 20, 27, 34, 41, 48 and 59. They identified sick young infants with PSBI signs and referred them to registered nurses at the health centres for further assessment and management. All infants continued to be assessed for all signs of PSBI at the community level by the CHWs and CHEWs, whether or not they were enrolled in a treatment trial.	CHWs made 10 scheduled home visits over the first 60 days after birth, ideally on days 0, 2, 6, 13, 20, 27, 34, 41, 48 and 59.
Management of infants	Infants identified with >1 sign of PSBI and enrolled in antibiotic treatment trials were managed according to trial protocols.^19^,^22^	Infants were managed according to standard care at the study sites.^23 24^ Blood and respiratory cultures were obtained from infants with signs of PSBI to identify the aetiology of infections.
Mortality assessment	The study outcome was the status of the child as alive or dead (all-cause) recorded by CHWs/CHEWs during home visits to assess infants for signs of PSBI.	CHWs assessed vital status at each home visit. Death cases were referred to supervisors of the verbal autopsy study, who conducted a verbal autopsy to determine the cause of death.
Young infants enrolled (N)	84 759 infants	63 017 infants
Young infant deaths (N)	587 deaths	1635 deaths

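### The third Cox age window starts at day 7 in its words but at day 0 in its label, so as labelled no Cox time frame isolates ages 7–59 days

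*Protocol article*

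**What the plan says.** In the protocol article, the section on Cox regression analysis first specifies an analysis over the whole follow-up: "finding a sign of PSBI from the first visit to the end of 60 days after birth". It then adds analyses in three age windows, each described in words and again by a bracketed day range:

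- earliest: "the first CHW visit to the end of day 3 (days 0 to <3"
- first week: "the first visit to the end of day 7 (days 0 to <7"
- late: "day 7 to the end of the 60th day (days 0 to <60"

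Elsewhere the article uses the bracketed range of the late window for the full follow-up age span. The abstract's methods paragraph speaks of signs identified "throughout the young infant period (days 0 to <60". The Introduction describes the WHO recommendation for "outpatient treatment of infants aged 7–59 days who present with isolated fast breathing". Nothing else in the article says which version of the late window applies.

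**The concern.** The late window is defined twice in one sentence, with different starting points. An analyst coding from the bracketed range and a reader relying on the words would attach different estimands to the same result.

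The first-week versus later contrast is at stake. If the range is followed, every first-week death that counts in the second window also counts in the third, and the two cannot be compared as early and late. The third analysis would also add little to the whole-period analysis, and the set of windows would hold no estimate for the 7–59 day band.

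**Working it through.** No sample size or power figure is involved. The check compares the days covered by the words with the days covered by the range, under each reasonable way of counting days.

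**Readings of the words**

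- A: birth is day 0, and the end of day n includes the day numbered n. Table 1 numbers visits this way (0, 2, 6, 13 and so on).
- B: the end of day n means n completed days, and a start at day 7 means age 7 completed days. The ordinal in the late window's own wording (60th) supports counting the end this way.
- C: every day is ordinal, so day 7 is the seventh day, numbered 6 when birth is 0.

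**Days covered (birth = 0)**

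| Window | Range | Words, A | Words, B | Words, C |
|---|---|---|---|---|
| Earliest | 0–2 | 0–3 | 0–2 | 0–2 |
| First week | 0–6 | 0–7 | 0–6 | 0–6 |
| Late | 0–59 | 7–60 | 7–59 | 6–59 |

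**Results**

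1. Late window: range and words agree under none of the readings. The range adds days 0–6 under A and B and days 0–5 under C. Under A the words also add day 60.
2. Earliest and first-week windows: range and words agree under B and C, and differ by one day each (day 3, day 7) only under A.
3. By range, the late window spans 60 days and contains all of days 0–6, the whole first-week window. By words under B it spans 60 − 7 = 53 days, does not overlap days 0 to <7, and together with them makes up days 0 to <60.

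**Possible size**

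Table 1 gives "587 deaths 1635 deaths" for AFRINEST and ANISA, so 587 + 1635 = 2222, not split by age. Let s be the share dying in the first week; s is not in the document and is assumed to lie between 0.3 and 0.8.

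- Events admitted by the range: up to 2222.
- Events admitted by the words: 2222 × (1 − s).
  - s = 0.3: 2222 × 0.7 ≈ 1555
  - s = 0.5: 2222 × 0.5 = 1111
  - s = 0.7: 2222 × 0.3 ≈ 667
  - s = 0.8: 2222 × 0.2 ≈ 444

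All are upper bounds, because deaths before a first health-worker visit drop out of the Cox analysis.

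**The case against.** The strongest reply is that this is a printing slip, 0 for 7, and that the words are clear enough. A second analysis from day 0 to day 60 would be largely redundant beside the whole-period one, and the 7–59 day band matches the guidance the paper discusses. Most of this stands: the words are the likelier intention. It does not settle the matter, because the first two windows both start at day 0, and a third window nested in the same way cannot be excluded from the text alone.

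Three stronger readings are tempting, and the document does not support them.

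- A reader might infer that all three windows contradict themselves. The first two do so only under reading A; under B and C their words and ranges agree. The convention is unstated, which is a lesser matter.
- A reader might infer that the late hazard ratios will be distorted by a known amount. That follows only if the range is used in place of the words, and the article gives neither deaths by age nor age-specific hazard ratios for this purpose. Any figure on that scale would rest on invented inputs.
- A reader might infer that all windows ought to be disjoint. The earliest lies inside the first-week window, apparently by design, and that is no error.

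It is also fair to say that the link between these windows and the fast-breathing guidance is drawn from the Introduction; the Cox section does not state it. How risk time after a sign found before day 7 is handled across the boundary can be left to the full analysis plan.

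**Conclusion.** The point holds for the third window. Its words and its range conflict under each of the three conventions, in the operative analysis text. If the range governs, first-week deaths enter the late estimate; if the words govern, they do not (under reading C, deaths on the seventh day still would). On the assumed first-week share of 30% to 80%, the choice moves up to about 667 (2222 − 1555) to 1778 (2222 − 444) deaths in or out of that analysis.

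The scope is limited to one age-specific part of one of three analysis types. The whole-period Cox, case-fatality and machine learning analyses are unaffected. That the words are the intention is an inference for the authors to confirm.

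**What to change.** If the words are right, change the bracketed range of the third window to days 7 to <60, with entry at day 7 or at the first visit if that is later. If a nested window from day 0 was meant, correct the words instead and add a separate window of days 7 to <60.

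In either case state the convention once: age in completed days, birth = day 0. The upper limits of the first two windows then plainly mean three and seven completed days, matching <3 and <7.

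The cost is one sentence. No new data are needed, and no other analysis changes.

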### Machine learning analysis

ML models will be trained to predict the risk of death for infants with signs of PSBI. The presence/absence of PSBI signs recorded over multiple visits, as well as available clinical and treatment data, will be used as input features. See supplemental table S1 (in online supplemental file 1) for a preliminary list of available predictors that are common to the ANISA and AFRINEST studies (which includes all predictors in AFRINEST) and supplemental table S2 (in online supplemental file 1) for a list of predictors available in the ANISA dataset. We will use two approaches. First, multivariate modelling will be applied to obtain precise contributions of each sign and combinations of signs to the mortality rate. In this approach, models will be built by applying standard ML models, specifically Elastic Net, XGBoost and Stabl.^33^,^35^ Presence/absence of PSBI signs at different times will be treated as separate features, and the model will predict the risk of death on a specific day given the signs on that day and in the previous 6 days.

Three models will be analysed, each specifying how the risk of death depends on PSBI signs with increasing levels of detail. We denote the predicted (dependent) variable as Y∈{0,1}

where

$$Y=\left\{ \begin{array}{l} 1,\;if\;infant\;dies\;in\;the\;7-day\;window\\ 0,\;otherwise \end{array}\right.$$

In our first (simplest) model 1, we will assume a standard logistic model for the probability of infant death given the signs in the previous 7 days.^36^ We include interaction terms between two different signs to quantify the effect of the presence of two signs on the probability of infant death. The probability that an infant dies given signs in the previous 7 days is then given by

$$\log\left(\frac{P\left(Y=1|X_{1},\ldots ,X_{p}\right)}{P\left(Y=0|X_{1},\ldots ,X_{p}\right)}\right)=\beta_{0}+\sum_{i=1}^{7}\beta_{i}X_{i}+\sum_{i=1}^{7}\sum_{j=2,\;j>i}^{7}\beta_{ij}X_{i}X_{j}+\sum_{i=8}^{p}\beta_{i}X_{i}$$

where input features $X_{i},i=1,\ldots ,7$are given by

$$X_{i}=\left\{ \begin{array}{l} 1,\;if\;sign\;i\;is\;present\;at\;any\;time\;during\;7\;days\\ 0,\;otherwise \end{array}\right.$$

and $X_{i},i=8,\ldots ,p$ are input features for each of the baseline covariates.

The output of the ML model will provide adjusted ORs for the risk of death for each sign and the interaction of signs. ORs for each sign *i* will be obtained as: $OR_{i}=e^{\beta_{i}}$. A limitation of model 1 is that the risk of death depends only on the presence/absence of each of the signs at any time during the 7-day window but does not account for the time lag between the sign and the outcome. Consequently, the probability in model 1 will be the same for two infants that died on different days but had the same signs.

In our second model, we will capture the day in the 7-day window when the death occurred, as follows. For each infant indexed by b that died on day $k_{b}\in \left\{0,\ldots ,6\right\},$ we define $k_{b}$ outcomes $Y_{bk}\in \left\{0,1\right\},k=1,\ldots ,k_{b}$

where

$$\begin{array}{l} Y_{bk}=\left\{ \begin{array}{c} 1,if\;k=k_{b}\\ 0,k§lt;k_{b} \end{array}\right.k=1,\ldots ,\;k_{b}. \end{array}$$

For infants that survived, we have $Y_{bk}=0,\text{for}\;k=0,\ldots ,6$.

We then consider model 2, which, similar to model 1, is a logistic model:

$$\log\left(\frac{P\left(Y_{bk}=1|X_{1},\ldots ,X_{p}\right)}{P\left(Y_{bk}=0|X_{1},\ldots ,X_{p}\right)}\right)=\beta_{0}+\sum_{i=1}^{7}\beta_{i}X_{ik}+\sum_{i=1}^{7}\sum_{j=2,\;j>i}^{7}\beta_{ij}X_{ik}X_{jk}+\sum_{i=8}^{p}\beta_{i}X_{i}$$

where $X_{ik},i=1,\ldots ,7$ denotes the presence or absence of sign *i* at any time before or at day k:

$$X_{ik}=\left\{ \begin{array}{l} 1,\;if\;sign\;i\;is\;present\;at\;any\;day\;before\;day\;k\;or\;at\;day\;k\\ 0,\;otherwise \end{array}\right.$$

In our third model, we capture the timing of each clinical sign. To achieve this, we consider separate features for the presence/absence of PSBI signs for each day:

$$\log\left(\frac{P\left(Y_{k}=1|X_{1},\ldots ,X_{p}\right)}{P\left(Y_{k}=0|X_{1},\ldots ,X_{p}\right)}\right)=\beta_{0}+\beta_{1}^{0}X_{1}^{k}+\beta_{1}^{-1}X_{1}^{k-1}+\ldots +\beta_{1}^{-6}X_{1}^{k-6}+$$

$$\beta_{2}^{0}X_{b}^{k}+\ldots \beta_{b}^{-6}X_{b}^{k-6}+\ldots +\beta_{7}^{-6}X_{7}^{k-6}+\sum_{i=8}^{p}\beta_{i}X_{i}$$

where input features $X_{i}^{k},i=1,\ldots ,7,k=0,\ldots ,6$ are given by

$$X_{ik}=\left\{ \begin{array}{l} 1,\;if\;sign\;i\;is\;present\;at\;any\;day\;before\;day\;k\;or\;at\;day\;k\\ 0,\;otherwise \end{array}\right.$$

In the case of model 3, 1-hot encoding will be used to construct matrix X containing all input features.

We will next perform a survival analysis to estimate the time to death. The standard approach is to apply the Cox proportional hazards model.^37^ In the case where a large number of covariates (and specifically in the case p§gt;N, where N denotes the size of the cohort), the Cox model can experience degenerate behaviour.^38^ To avoid this problem and handle a large number of covariates, we will use a regularised Cox proportional hazards model regularised by Elastic Net.^38^ The Cox model assumes semiparametric hazard in which the hazard for patient i at time t is:

$$h_{i}\left(t\right)=h_{0}\left(t\right)e^{X_{i}^{T}\beta }$$

where $X_{i}=\left(X_{i,1},\ldots ,X_{i,p}\right)$ is a vector of covariates at time t, β is a vector of coefficients of length p and $h_{0}(t)$ is the shared baseline hazard. The vector of coefficients, β, is determined by maximising the partial likelihood

$$L\left(\beta \right)=\prod_{i=1}^{m}\frac{e^{X_{j\left(i\right)}^{T}\beta }}{\sum_{j\in R_{i}}e^{X_{j}^{T}\beta }}$$

which in this case will be subject to the Elastic Net constraint that combines Lasso^39^ and Ridge Regression.^40^

for some threshold *t*. Here, m denotes the total number of time instances in the observation window, j(i) denotes observations failing at time i and $R_{i}$ is a set of indices for which failure occurs at or after time i.

Equivalently, coefficients β will be determined by solving the following:

$$\hat{\beta }={argmax}_{\beta }\left[\frac{2}{N}\left(\sum_{i=1}^{m}X_{j\left(i\right)}^{T}\beta -\log\sum_{j\in R_{i}}e^{X_{j}^{T}\beta }\right)-\lambda P_{\lambda }\left(\beta \right)\right]$$

where

$$P_{\lambda }\left(\beta \right)=\alpha \sum_{i=1}^{p}\left|\beta_{i}\right|+\frac{1}{2}\left(1-\alpha \right)\sum_{i=1}^{p}\beta_{i}^{2}$$

is the Elastic Net penalty. The R package glmnet^41^ will be used for the ML analysis.

The results from these analyses will enable us to gain additional insights, particularly from ML analysis, into combinations of signs of PSBI and potentially other factors that identify young infants with particularly heightened risk for mortality. This information will be taken into account in considering modifications to IMCI for young infants. We will also consider the development of an app—starting, for example, with fast breathing in the first week after birth—to be used by CHWs to guide the management of infants based on information that is useful in predicting risk for mortality.

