##### Case fatality analysis

AFRINEST data were initially analysed using case fatality analysis, as described previously.^28^ This analysis has the advantage of simplicity of interpretation but lacks consideration of the time-varying risk of mortality. We will use data from the AFRINEST and ANISA studies for infants up to 2 months of age with at least one visit to assess the presence of clinical signs and the outcome following that visit. We will assume infants were alive for all visits until and unless a death is recorded. The case fatality rate will be calculated by sign or a combination of signs as the percentage of young infants who die within 7 days after showing that sign or a combination of signs of PSBI, divided by the total number of young infants who had shown that same sign or a combination of signs during their previous (reference) visit. We specify a 7-day window period to avoid the risk of misclassification or recall bias when no visit data were available for the extended period.

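### The 7-day sign-to-death window is not defined consistently across the analyses, and under the ML lag 0–6 rule a death on the next weekly visit day can be coded sign-free

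*Protocol article*

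**What the plan says.** All three mortality analyses use a window of about 7 days between a sign and a death, but each words it differently.

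- **Case fatality analysis:** the rate is the "percentage of young infants who die within 7 days after showing that sign", referred back to the visit at which the sign was shown.
- **Cox regression analysis:** "The period of risk for mortality will be defined as extending for 7 days after finding a sign of PSBI". For its age frames, the same section writes "the first visit to the end of day 7 (days 0 to <7", which is days 0 to 6.
- **Machine learning analysis, general rule:** "the model will predict the risk of death on a specific day given the signs on that day and in the previous 6 days".
- **Model 1:** a logistic model "for the probability of infant death given the signs in the previous 7 days", without saying whether the prediction day is one of the seven.
- **Model 2:** the day of death runs from 0 to 6. The sign feature is 1 if the sign was present on day k or any day before it.
- **Model 3:** the equation has lags from k to k-6, but the feature definition printed beneath it is the cumulative one from model 2.

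In Table 1 (clinical sign assessment), ANISA home visits are scheduled "ideally on days 0, 2, 6, 13, 20, 27, 34, 41, 48 and 59". AFRINEST used the same days.

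**The concern.** A one-day difference at the edge of a window is usually trivial. Here the disputed day is the next scheduled visit day for most of the follow-up period.

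Take an infant with a sign on day 6 who dies on day 13 before the worker arrives. On the ordinary reading, case fatality counts this death for the sign. Under the lag 0–6 rule the look-back is days 7 to 13 and contains no completed scheduled visit. Every sign indicator then takes its default value of 0, and the death enters as sign-free. An infant who survives to be seen on day 13 has an assessment at lag 0. On those days the quality of the exposure data therefore depends on the outcome.

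Two things are at stake. First, if the ML odds ratios differ from the case-fatality or Cox results, a reader cannot tell a difference in method from a difference in window. Second, moving exposed deaths into the sign-free group lowers the sign odds ratios. The Machine learning analysis section says that the results, particularly those from ML, will be considered in modifying the IMCI guidance.

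**Working it through.** The plan gives no figure to reproduce, so the check sets the definitions side by side and enumerates the visit schedule.

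**Step 1. Last day after the sign that each analysis covers.**

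| Analysis | Last day covered | How firm |
|---|---|---|
| Case fatality | 7 | ordinary reading; inclusion of day 7 not stated |
| Cox | 7 | weaker reading; could be coded as days 0 to <7 |
| ML general rule | 6 | explicit |
| Model 1 | 6 or 7 | not stated |
| Model 2, outcome days | 6 | explicit |
| Model 2, sign feature | no lower bound | explicit |
| Model 3, lags in the equation | 6 | explicit |
| Model 3, printed feature | no lower bound | conflicts with the equation |

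**Step 2. Visit gaps (Table 1).** Days 0, 2, 6, 13, 20, 27, 34, 41, 48 and 59 give gaps of 2, 4, 7, 7, 7, 7, 7, 7 and 11 days. Six of the nine are exactly 7.

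**Step 3. A death exactly 7 days after a visit with a sign.** For a sign on day s, set d = s + 7 and list the scheduled visits from d-6 to d-1.

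| s | d | Visits in the look-back before d | Visit due on d? |
|---|---|---|---|
| 0 | 7 | 2, 6 | no |
| 2 | 9 | 6 | no |
| 6 | 13 | none | yes |
| 13 | 20 | none | yes |
| 20 | 27 | none | yes |
| 27 | 34 | none | yes |
| 34 | 41 | none | yes |
| 41 | 48 | none | yes |
| 48 | 55 | none | no |

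The contrast between deaths and survivors arises on six days: 13, 20, 27, 34, 41 and 48. In the first week another visit always falls in the look-back. On day 55 no visit is due, so a survivor's look-back is as empty as that of an infant who died. Unscheduled contacts could fill some of these gaps.

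**Step 4. What happens to the death.** Under the general rule and model 3's lags, all sign terms are 0. If model 2 is anchored at the reference visit, a day-7 death lies outside its days 0 to 6 and is not counted as a death in that window. If the cumulative feature is applied literally and not reset, the earlier sign is still 1 and this miscoding does not occur.

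**Step 5. Size.** The article gives no distribution of the lag from sign to death. Assume the daily risk after a sign is multiplied by r each day. The share of deaths at lag 7 among lags 0 to 7 is r^7 / (1 + r + … + r^7).

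- r = 1 (flat): 1/8 = 12.5%
- r = 0.9: 8.4%
- r = 0.7: 2.6%
- r = 0.5: 0.4%

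For a given r, this share is a ceiling on the sign-exposed deaths recoded: it counts every lag-7 death, whereas only those before the visit, on the six days above, lose their sign.

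**The case against.** The strongest counter-argument is that no section says the case-fatality or Cox window includes day 7. The Cox section writes the end of day 7 as days 0 to <7 for its age frames. If the post-sign window follows that habit, it covers days 0 to 6 and matches the ML lags exactly. This stands in part, and it rules out calling the difference a proven contradiction. It does not remove the problem, because the empty look-back comes from the ML rule itself and remains under either reading. So does the unreconciled pair of 6 and 7 previous days within the ML section.

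It can also be said that exact day boundaries belong in a full analysis plan. That would hold if the article were silent, but it fixes the lags in a sentence and in formulas, and these disagree.

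The planned 14-day sensitivity analysis, with similar 7- and 14-day results reported for ANISA, makes a large effect less likely. ANISA supplies 1635 of the 1635 + 587 = 2222 deaths (74%). That analysis concerns Cox, however, and does not test how the ML features are coded.

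A reader might infer more than the document supports:

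- **That every ML model stops at day 6.** Model 1 and the cumulative features do not clearly do so.
- **That the sign odds ratios shrink by a known factor.** Factors of about 0.75 to 0.90 can be obtained, but only by assuming flat risk and that 30% to 50% of deaths are sign-exposed. The article gives neither.
- **That the odds ratios for ages 7–59 days are specifically affected.** No age-stratified ML model is described. In an all-age model, first-week deaths dilute the effect.
- **That AFRINEST deaths are dated to the visit that recorded them, making the loss far larger.** Table 1 says only that vital status was recorded at home visits, and the studies were selected for having recorded the timing of deaths.

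**Conclusion.** The point holds as an inconsistency in definition with a concrete consequence for coding. The general ML rule, model 2's outcome days and model 3's lags stop at day 6. Case fatality, and less clearly Cox, read as reaching day 7. Model 1 and the printed features for models 2 and 3 fit neither cleanly.

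On six scheduled visit days the lag 0–6 rule leaves a pre-visit death without an assessment while a survivor has one. Where such a death followed a sign, it is coded sign-free and the sign odds ratio is biased downward. Under model 2's outcome window it is lost instead.

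The affected share of window deaths ranges from about 0.4% to 12.5% across the assumed risk patterns. This rests on adherence to the schedule, on few unscheduled contacts, and on the lag 0–6 rule being applied as stated. It is a modest point, worth correcting because the correction is cheap.

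**What to change.** State one sign-to-death window for all three analyses that includes day 7 after the sign, and say whether the day of the sign counts.

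In the ML section:

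- let the look-back cover signs found 1 to 7 days before the prediction day, plus the same day only if the visit preceded the death;
- index model 3 from k-1 to k-7, with day-specific features in place of the cumulative definition now printed;
- run model 2 over days 1 to 7 after the reference visit;
- bring model 1's wording into line.

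The cost is a few sentences and a small change to feature construction. No new data are needed.

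### The adjusted ORs for signs and sign pairs are to be read from penalised coefficients, so they are pulled towards 1 by an amount that depends on unstated tuning

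*Protocol article*

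**What the plan says.** All of this is in the protocol article, under Machine learning analysis.

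- The multivariate approach is meant "to obtain precise contributions of each sign and combinations of signs to the mortality rate".
- Its tools are fixed: "models will be built by applying standard ML models, specifically Elastic Net, XGBoost and Stabl".
- For model 1, "we will assume a standard logistic model for the probability of infant death". It has seven sign main effects, all pairwise products of signs, and baseline covariates. On the products the article says: "We include interaction terms between two different signs to quantify the effect of the presence of two signs on the probability of infant death".
- After the model 1 equation comes the reporting rule: "The output of the ML model will provide adjusted ORs for the risk of death for each sign and the interaction of signs". The formula printed for a single sign is `exp(beta_i)`.
- Model 2 has the same main-effect and interaction structure. Model 3, as written, has no sign-by-sign interactions.
- The Elastic Net penalty, with its absolute-value and squared terms, is written out for the later Cox model. The R package glmnet is named for the ML analysis as a whole.

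Two other sections bear on the point. Cox regression analysis plans covariate-adjusted estimates for each sign by itself, for the sign together with at least one other, and for other signs only, each against no sign. Case fatality analysis gives seven-day percentages by sign or combination, with no adjustment described.

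**The concern.** The rule treats the exponent of a penalised coefficient as an ordinary adjusted OR. The penalty trades bias for prediction accuracy: it moves every coefficient towards zero and can remove the weaker ones. An OR of 1.0 from such a fit may mean no association, or an association too small or too rare to survive the penalty. The reported number does not tell the two apart.

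That matters for the study's purpose. The Introduction wants to find infants whose signs carry a lower mortality risk, and shrinkage towards 1 makes a moderate-risk sign look closer to no risk. It matters most for specific pairs of signs, because no other planned analysis gives an adjusted effect for a named pair.

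A smaller point is labelling. With pairwise products in the model, `exp(beta_i)` compares sign i alone with no sign, and the article does not say so next to the formula.

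**Working it through.** The article states no figure for this quantity, so there is none to reproduce. The check has three parts.

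**1. Size of the problem (Table 1).** Infants: 84,759 + 63,017 = 147,776. Deaths: 587 + 1,635 = 2,222, or 2,222 / 147,776 = 1.5%. Sign pairs: 7 × 6 / 2 = 21, so signs and pairs make 28 terms. That is at most 2,222 / 28 ≈ 79 deaths per term before baseline covariates. It is an upper limit, since the models count deaths in a seven-day window. An unpenalised fit looks feasible for main effects, though some pairs may be sparse.

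**2. Shrinkage.** glmnet minimises the negative mean log-likelihood plus `lambda × [alpha × sum|beta| + (1 − alpha)/2 × sum beta²]`. The first penalty term can set a coefficient to exactly zero; both pull it inwards.

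An illustrative simulation used 147,776 infants, 2,252 simulated deaths, seven signs and 21 interactions, with standardised predictors as in glmnet. These inputs are assumptions, because the article gives none of them: prevalences 0.3% to 5%, true ORs 1.3 to 8, every interaction OR 0.7, and positively correlated signs. One data set was drawn. Results with alpha = 1:

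| lambda / lambda_max | true 1.3 | true 2 | true 3 | true 4 | true 8 | interactions kept (of 21) |
|---|---|---|---|---|---|---|
| 0.5 | 1.00 | 1.00 | 1.00 | 1.43 | 3.79 | 0 |
| 0.2 | 1.00 | 1.09 | 1.73 | 2.46 | 5.49 | 1 |
| 0.1 | 1.00 | 1.40 | 2.12 | 2.89 | 6.08 | 8 |
| 0.05 | 1.08 | 1.64 | 2.49 | 3.25 | 7.12 | 14 |
| 0.02 | 1.18 | 1.82 | 2.79 | 3.62 | 7.80 | 17 |
| 0.01 | 1.22 | 1.90 | 2.91 | 3.75 | 8.05 | 20 |
| 0.001 | 1.26 | 1.96 | 3.04 | 3.86 | 8.28 | 21 |

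With alpha = 0.5 the results were almost the same (at 0.1: 1.00, 1.38, 2.08, 2.82 and 5.97).

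The last row is close to an unpenalised fit, so it serves as the comparator. For the sign with true OR 2, the share of the log OR kept is ln 1.40 / ln 1.96 = 0.336 / 0.673 = 50% at 0.1, and ln 1.90 / ln 1.96 = 0.642 / 0.673 = 95% at 0.01. At 0.1, 21 − 8 = 13 interaction ORs would be reported as exactly 1 although each is truly 0.7.

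A second simulation (about 1,900 deaths, four replicates, other assumed inputs) chose lambda by minimum cross-validated deviance. True ORs of 2, 3, 5 and 6 averaged 1.72, 2.72, 4.87 and 5.24, so the bias under that light tuning was small.

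**3. Meaning of the coefficient.** From the model 1 equation, the log OR for sign i given the other signs is `beta_i + sum over j of beta_ij × X_j`. Take OR 2 for sign 1 and 5 for sign 2:

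- interaction OR 0.5: sign 1 when sign 2 is present, 2 × 0.5 = 1; both v none, 2 × 5 × 0.5 = 5
- interaction OR 1: 2 × 1 = 2; both v none, 10
- interaction OR 2: 2 × 2 = 4; both v none, 20

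`exp(beta_1)` is 2 throughout.

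**The case against.** The other side has real substance.

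- **Tuning may be light.** Neither lambda, alpha nor a selection rule is given, and an article may leave these to a fuller document. With this many deaths a prediction-optimal lambda may leave little bias, as the second simulation shows. This stands: the size of the bias is open. What does not depend on tuning is the direction, and the fact that a prediction criterion, not an estimation one, would set it.
- **Other analyses cover single signs.** The Cox analysis already gives conventional adjusted estimates for a sign by itself, and case fatality is tabulated by combination. This stands and limits the consequence. It does not cover adjusted effects of named pairs.
- **The interaction formula is not wrong.** `exp(beta_i)` is a valid contrast of one sign alone with no sign. Interaction ORs are promised too, so pair ORs can be rebuilt. This stands; the remaining fault is a missing label.
- **The logistic model might be unpenalised.** Calling it standard allows that reading. But the same section says the models are built with the three named tools and later names glmnet, so the penalised reading is the more natural one.
- **The OR formula may never have been meant for XGBoost.** That is possible, since it follows the logistic equation. The text nevertheless attributes the ORs to the ML output without saying which of the three methods supplies them.

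A reader might go further and infer that penalisation is unjustified here because predictors cannot outnumber infants. The documents do not support that as a criticism of these ORs. The remark, "where N denotes the size of the cohort", belongs to the later Cox survival model, and the reason given there is more broadly a large number of covariates.

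**Conclusion.** The point holds in a limited form. As written, the plan would report as adjusted ORs quantities that are biased towards 1, and one of the three named methods, if tree-based, gives no such coefficient. In the illustration the loss for a true OR of 2 ran from about 5% of the log OR (lambda ratio 0.01) to about half (0.1), and to all of it at 0.5. These figures show a range under assumed prevalences and effects. They do not predict this study's result.

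A reader might infer that low-risk signs will be declared harmless, or that moderate ORs will collapse to 1. The documents do not support that. It would need a heavy penalty that the article never specifies, and single-sign conclusions can also draw on the Cox analysis. Nor has it been shown that penalisation would make estimates for rare signs unstable; few deaths alone could do that.

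The exposure is greatest for specific pairs of signs, where the ML section is the only source of adjusted effects. The change is worth making before the ORs are reported.

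**What to change.** - Keep Elastic Net, XGBoost and Stabl for prediction and for selecting signs and combinations.
- Take the reported ORs and intervals from an unpenalised logistic fit of model 1, with Firth's method where pair cells are sparse. Alternatively, leave all seven sign main effects and all 21 pairwise interactions unpenalised within the Elastic Net fit.
- Compute the intervals so that they allow for repeated records from the same infant, for example by resampling infants.
- Label `exp(beta_i)` as *sign i alone v no sign*, and report `exp(beta_i + beta_j + beta_ij)` as *signs i and j together v no sign*.
- Reword the reporting sentence so that it names the fit that supplies the ORs.

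The cost is one extra model fit and a few lines of text. The downside is wider intervals for rare combinations, which reflects what the data can support.
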